|                                                      | 
 
Concomitant non-pharmacological interventions
 
                                                                                                                                                                                                                                                                                                                                                                                                                                                                                                                                                                                                                                                                                                                                                                                                                                                                                                                                                                                                                                                    |
| Safety                                        | Information about suspected adverse reactions (SAR) and serious adverse events (SAE) will be collected at 4, 8 and 12 weeks. Data will be evaluated and assessed continuously throughout the study by the study investigators for each patient to determine whether there is any relationship to the study interventions.                                                                                                                                                                                                                                                                                                                                                                                                                                                                                                                                                                                                                                                                                                                                                                                                                          |

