# 9 ASSESSMENT OF SAFETY

M-sense Migräne is a CE marked medical device with an established risk management which will also take place during the study period.

Safety outcomes defined for the study are the number of participants with serious adverse events, suspected adverse reactions and serious suspected adverse reactions.

All suspected adverse reactions and all serious adverse events will be listed and evaluated. An adverse event is any undesirable experience associated with the use of a therapy in a patient. The event is serious and should be reported when the patient outcome is: results in death or is life-threatening, requires inpatient hospitalization or prolongation of existing hospitalization, results in persistent or significant

disability/incapacity, or results in a congenital anomaly/birth defect (Good-Clinical-Practice-Verordnung, GCP-V).

A suspected adverse reaction in our study is defined as an effect that the app user directly associated (self reported) with the app use. For “serious” the same categories mentioned above are used.

In this study, patients will be asked about suspected adverse reactions and serious adverse events within the app (see Table 3).

In addition, we will collect serious suspected adverse reactions (patients will be informed during informed consent and by the app to call the study office in case they assume to have a serious suspected adverse reactions).

A causality assessment of the serious adverse event with respect to the trial intervention (see Table 3 based on the terms given in the ICH E2A guideline) will be performed. Any event assessed as possibly, probably or definitely related is classified as related to the trial intervention.

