## 11.10 Analyses of safety outcomes

All safety variables will be tabulated (in total and per treatment group). Reported are number of participants with suspected adverse reactions, serious suspected adverse reactions, and adverse events, number of participants who withdraw from the study due to suspected adverse reactions. Categorical variables are reported using frequency and percentage, continuous variables are reported by giving descriptive measures (mean, standard deviation/standard error, quartiles, and range). The evaluation of safety endpoints is performed with the safety population.

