#### 10.7 ANALYSIS OF SAFETY

Based on the safety population all safety variables will be tabulated (in total and per treatment group for adverse events). We will display the number of patients with serious adverse events, suspected adverse reactions, and serious suspected adverse reactions, and the number of patients who withdraw from the study due to safety concerns. Categorical variables are reported using frequency and percentage, continuous variables are reported by giving descriptive measures (mean, standard deviation/standard error, quartiles, and range). Groups will be compared by Chi-square or Wilcoxon rank test.

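### As described, safety collection covers serious events in both arms and self-attributed reactions in the app arm only, so protocol 11.10's per-group table does not match it and non-serious, non-headache harm cannot be compared between arms

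*Combined protocol and SAP*

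**What the plan says.** **Collection.** The protocol synopsis (Safety) says: "Information about suspected adverse reactions (SAR) and serious adverse events (SAE) will be collected at 4, 8 and 12 weeks". Protocol section 9 says the same of the in-app questions: "In this study, patients will be asked about suspected adverse reactions and serious adverse events within the app (see Table 3"; the table it points to is the causality tool, so the questions themselves are not shown. A SAR "in our study is defined as an effect that the app user directly associated (self reported) with the app use". Users are told to report serious SARs by calling the study office. The log described in section 9 holds SAEs and SARs.

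**Definitions.** Section 9 defines the wider term without requiring seriousness: "An adverse event is any undesirable experience associated with the use of a therapy in a patient". It then fixes the outcomes: "Safety outcomes defined for the study are the number of participants with serious adverse events, suspected adverse reactions and serious suspected adverse reactions". Protocol 6.4 lists the same three.

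**By arm.** SAP 6.4 measures SAEs in both groups and SARs in the M-sense group only. SAP Table 2 compares the arms on SAEs. SAP Table 3 describes SARs in the M-sense group.

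**Reporting.** Protocol 11.10 tabulates all safety variables in total and per group: "Reported are number of participants with suspected adverse reactions, serious suspected adverse reactions, and adverse events". SAP 10.7 says "all safety variables will be tabulated (in total and per treatment group for adverse events", and its next sentence lists SAEs, SARs and serious SARs.

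**The concern.** Protocol 11.10 names two per-group items that the described collection does not supply as worded. One is participants with adverse events, a wider set than SAEs under section 9's own definition. The other is SARs, for which the SAP plans no control-arm data.

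Behind the wording lies a question of content. The app gives exercise instructions, training plans, stretching and self-massage (protocol 7.1). A plausible harm from these is minor, such as a muscle strain. It would be recorded as a safety event only if the user ascribed it to the app, and then with no control figure beside it. The trial is meant to support a listing decision, and events that nobody asked about cannot be recovered reliably afterwards. Without a change, the safety comparison rests on SAEs plus whatever shows in the headache and medication diary.

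**Working it through.** **1. The plan's own figure.** The sample size is the only design figure available here. With a difference of 1.27 days, SD 4.20, two-sided 5% and 80% power (SAP 7), the normal approximation is n = 2 × (1.960 + 0.842)² × (4.20/1.27)² = 171.7, so 172 per group. The t-test calculation gives 172.65, so 173, as stated. Power at 173 is 80.1%. The figure reproduces, and the safety point does not depend on it.

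**2. What 11.10 reports, set against what is collected.**

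| Item in protocol 11.10, per group | M-sense arm | Control arm |
|---|---|---|
| SAR | Asked at weeks 4, 8, 12 | Not measured (SAP 6.4, SAP Table 3) |
| Serious SAR | Calls to the study office | No SAR measure planned in the SAP |
| Adverse events, read literally | No source for non-serious events the user does not link to the app | No source for non-serious events |
| Adverse events, read as SAEs | Asked at weeks 4, 8, 12 | Asked at weeks 4, 8, 12 |

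The last reading is the more likely. 11.10 as written omits SAEs, although section 9 makes them a safety outcome, and inserting the word 'serious' restores exactly the three outcomes of section 9 and SAP 10.7.

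**3. What remains on that reading.** Both apps ask a daily headache question (SAP 6.1). Headache days, migraine days, moderate/severe headache days, acute-medication days and triptan days are compared between arms for each four-week period (SAP 6.2, SAP Table 2; for migraine days, weeks 9 to 12 are the primary outcome). Worsening of the target condition is therefore comparable. Events that are non-serious, not headache and not linked by the user to the app have no planned question in either arm. Those the user does link to the app have no control figure.

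**4. Illustrative size.** Every event rate here is an assumption. With 173 per arm, two-sided 5%, 80% power and the arcsine method, the detectable rate p₂ satisfies 2·arcsin√p₂ = 2·arcsin√p₁ + 2.802 × √(2/173), where the last term is 0.301.

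| Assumed control SAE rate | Expected patients per arm (173 × rate) | Detectable rate in the other arm |
|---|---|---|
| 0.5% | 0.9 | 4.8% |
| 1% | 1.7 | 6.2% |
| 2% | 3.5 | 8.3% |
| 3% | 5.2 | 10.2% |

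For a neutral any-event question, the 95% CI half-width for the risk difference is 1.96 × √(2p(1−p)/173), with both arms at p:

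| Assumed background p | Detectable rate | Rise (points) | CI half-width (points) |
|---|---|---|---|
| 10% | 20.7% | 10.7 | 6.3 |
| 20% | 33.2% | 13.2 | 8.4 |
| 40% | 55.0% | 15.0 | 10.3 |

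**The case against.** **The table.** A reader might infer that the 11.10 safety table cannot be produced. The documents do not support that. The SAP says it substitutes the evaluation concept, SAP 10.7 lists SAEs where 11.10 says adverse events, and SAP Table 2 sets out an SAE comparison that has data in both arms. The likely fault is one dropped word. What stands is that 11.10 still promises SARs per group, while the SAP measures them in one group.

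**No harm data at all.** A reader might also infer that SAEs are the only between-arm measure, or that non-serious harm is not recorded at all. That fails for worsening headache, which is recorded daily and compared. Reasons for withdrawal, contact with the study office and the count of withdrawals for safety concerns may reveal further events. They miss anyone who has a minor injury and stays in.

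**Proportionality.** The plan gives reasons for light collection: a CE-marked class I device used within its purpose, no significant risk expected, and a previous study in which the intervention was not associated with serious adverse events. This is a fair defence of the design. It bears mainly on serious harm and leaves non-serious harm open. That users would ascribe a strain to the activity and not to the app is plausible, but the documents do not show it.

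**Evidence.** The safety forms are not in the documents; their content is inferred from the synopsis, protocol section 9 and SAP 6.4. The trial is not powered for safety, so the detectable differences show no error in the plan.

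**Conclusion.** The point holds in a limited form. Protocol 11.10 does not agree with SAP 6.4 on SARs by arm, and its adverse-event item is either a slip for SAEs or has no data source. On either reading, non-serious harm other than headache worsening cannot be compared between arms.

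The size cannot be fixed from the documents. On assumed SAE rates of 0.5% to 3%, about 1 to 5 patients per arm would have an SAE, and only a rise to about 5% to 10% would be detected with 80% power. On assumed backgrounds of 10% to 40%, a neutral question would estimate the risk difference to within about 6 to 10 points. These figures are illustrative only.

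The conclusion assumes that the forms match their description. It does not touch the primary analysis, and it does not show that the app is unsafe or that the planned SAE table is wrong. The question proposed below is a cheap improvement; the wording reconciliation is needed in any case.

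**What to change.** **Preferred.** Put one neutral question first in the existing week 4, 8 and 12 safety forms, worded identically in both apps: *Have you had any new or worsened health problem or injury since the last form?* Follow it with the seriousness item in both arms, and with the app-attribution item where SARs are measured. Add to SAP 6.4 and SAP Table 2 the number of patients with any adverse event per arm over 12 weeks, with risk difference and 95% CI, in the safety population.

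**In either case.** Reconcile protocol 9 and 11.10 with SAP 6.4 and 10.7 on two matters: whether the per-group item is adverse events or SAEs, and that SARs are measured in one arm. If the question is declined, change 11.10 to SAEs and state that non-serious, non-headache harms are not compared between arms.

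**Cost.** One question at three existing prompts and one table row, with no new visit. Unrelated minor events in both arms must be logged: at assumed rates of 10% to 40%, about 35 to 138 of 346 patients (346 × 0.10 to 346 × 0.40). Section 9 asks for the causality assessment only for serious events, but the synopsis speaks more broadly of assessing relationship for each patient, so the text should say that minor events are logged without it. Because the trial is open-label, reporting may still differ by arm even with identical wording, and the new row should be read with that in mind.

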|                                   | health-related quality of life, safety, adherence, migraine-specific health literacy, and headache management self-efficacy of M-sense users.                                                                                                                                                                                                                                                                                                                                                                                                                                                                                                                                                                                                                                                               |
| Study design               | This is a two-armed, open-label, parallel-group, randomized, controlled study. Patients will be randomly allocated to one of the two groups in a 1:1 ratio to gain access either to the full M-sense Migräne app or the Control study app with only data input features. For motivational reasons the control group participants will gain access to the full M-sense Migräne app after 12 weeks. This additional data and the 24-weeks follow-up in the intervention group will not be part of the DiGA-study.                                                                                                                                                                                                                                                                                             |
| Interventions and controls | Intervention group: M-sense Migräne app for 12 weeks.
Control group: Control study app that only includes data input features (as a diary visible for one week without attack classification) and questionnaires. There will be no app interventions and no data will be feedbacked to the patients.                                                                                                                                                                                                                                                                                                                                                                                                                                                                                       |

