| Study procedures                              | The pre-screening of potential study participants will be carried out by a web page. In case of eligibility a code for usage of the study app is offered. In app informed consent on privacy aspects will be obtained. An anonymous 28 days baseline assessment will follow, which assesses the eligibility for the study. Close to the end of the baseline phase in a video consultation with a physician the migraine diagnosis will be confirmed, the main study eligibility will be checked and the informed consent will be obtained. Eligible patients receive a code from the physician. After participants complete the baseline phase eligibility criteria will be checked within the app (migraine days $\geq 3$ , filling in of the diary, no medication overuse). Eligible participants will then be asked within the app to enter the code received by the physician, participants will then be randomized within the app. They will participate in the DiGA study for 12 weeks according to treatment allocation. After the end of the DiGA study both groups will be able to use the app for further 12 weeks in a follow-up study. |
| Time points of data assessment                | Data of all endpoints are documented within the apps. For symptoms and medication intake daily, for other secondary outcomes at baseline and after 12 weeks (+ 12 weeks as follow-up in addition to the DiGA-study), for safety additionally after 4 and 8 weeks.                                                                                                                                                                                                                                                                                                                                                                                                                                                                                                                                                                                                                                                                                                                                                                                                                                                                                  |

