## 4 INVESTIGATION AND PROCEDURES

### 4.1 Overall study design

This is a two-armed, open-label, parallel-group, randomized, controlled trial. Potential study participants will be invited to participate in a 28-days baseline phase in which data on headache days and migraine attacks will be collected. This data will be used for the eligibility check. Furthermore, a physician (via video consultation) will inform about the study, validate the patient-reported migraine diagnoses and obtain the informed consent from study participants. After final informed consent and verification of the patient's eligibility for the study in the video consultation, patients will be randomly allocated to one of the two groups in a 1:1 ratio to gain access either to the full M-sense Migräne app or the control study app with only data input features (only as a diary visible for one week without attack classification with daily headache question and questionnaires, no app interventions and no feedback on data or behavior). The primary outcome will be the migraine days per month (defined as 28 days in weeks 9 to 12).

The DiGA-study will be completed after 12 weeks follow-up per study participant.

Additional data will be collected afterwards. Then both groups receive the full M-sense Migräne app and use the intervention for 12 weeks (see Figure 1). This will allow to gather data over 24 weeks in the intervention group and increase the motivation in the control group to participate in the study and to provide data over 12 weeks without access to the intervention.

[figure not shown]

Figure 1. Study flow and design of RCT

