| HALT-30                                   |                     | x                       |                                            |       |   | x  | x                                          |
| Migraine specific health
literacy      |                     | x                       |                                            |       |   | x  |                                            |
| Medication use                            | x                   |                         | x                                          |       |   |    |                                            |
| Use of app interventions                  |                     |                         | x #                             |       |   |    | x #                             |
| Safety measures                           |                     |                         |                                            | x     | x | x  | x                                          |

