### 10.3 Randomization

Eligible participants will then be asked by the app to enter the study code received from the physician and will be randomized within the app. They participate in the DiGA study for 12 weeks according to their treatment allocation. After the end of the DiGA study the intervention group keeps the M-sense Migräne app and the control will also receive access to all the features of the M-sense Migräne app. Both groups will participate in a 12-weeks in a follow-up study.

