### 6.4 SAFETY MEASUREMENTS

In both groups:

- Number of patients with a serious adverse event during the first 4 weeks, second 4 weeks, and third 4 weeks, and in total.
- Counts of serious adverse events during the first 4 weeks, second 4 weeks, and third 4 weeks, and in total.

In the M-sense Migräne app group only:

- Number of patients with a suspected adverse reaction during the first 4 weeks, second 4 weeks, and third 4 weeks, and in total.
- Counts of suspected adverse reactions during the first 4 weeks, second 4 weeks, and third 4 weeks, and in total.
- Duration of suspected adverse reaction.

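### Control patients' first 12 weeks on the full app carry one scheduled safety question, at the 24-week point, against three in the intervention arm

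*Combined protocol and SAP*

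**What the plan says.** On exposure, the documents agree. The synopsis (Study design) states that "the control group participants will gain access to the full M-sense Migräne app after 12 weeks". Protocol section 10.3 repeats that after the DiGA study "the control will also receive access to all the features of the M-sense Migräne app", and section 4.1 gives the length: "Then both groups receive the full M-sense Migräne app and use the intervention for 12 weeks".

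On safety questions, the synopsis row on time points of data assessment reads "after 12 weeks (+ 12 weeks as follow-up in addition to the DiGA-study), for safety additionally after 4 and 8 weeks". Protocol Table 1 marks the safety row at weeks 4, 8 and 12 and in the 24-week follow-up column. SAP Table 1 has the same four marks, with its follow-up column flagged as outside that SAP. The synopsis Safety row is narrower: information on suspected reactions and serious adverse events "will be collected at 4, 8 and 12 weeks", with no follow-up point.

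On reporting, SAP section 6.4 lists, for the M-sense group only, "Number of patients with a suspected adverse reaction during the first 4 weeks, second 4 weeks, and third 4 weeks, and in total". Protocol section 9 has patients asked inside the app, with a phone call to the study office for serious suspected adverse reactions. Section 5.5 adds in-app information on how to contact the office about safety concerns.

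**The concern.** The three early safety questions fall at the start of exposure in one arm and before any exposure in the other. In the intervention arm, weeks 4, 8 and 12 cover the first 12 weeks with the relaxation, training and acute-pain content. In the control arm the same three questions are answered while the patient holds an app without that content. When the content arrives, no question is scheduled until the 24-week point.

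At stake is the solicited safety information from the second group of new users. A non-serious suspected reaction in a control patient's first weeks on the full app may not be asked about until up to 12 weeks later. It may never be reported if the patient has stopped by then. The same holds for a serious adverse event that the patient does not attribute to the app. The details most exposed to delay are ones the plan wants: time relation and improvement after stopping (the causality tool, protocol Table 3) and duration of suspected reactions (SAP Table 3).

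**Working it through.** This is schedule arithmetic; no sample size or power figure enters it, and the plan states no figure to reproduce.

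**Inputs**
- Scheduled safety questions, in weeks since randomization: 4, 8, 12 and 24 (protocol Table 1; synopsis, time points).
- Start of full-app exposure: week 0 in the intervention arm; week 12 in the control arm (synopsis; sections 4.1 and 10.3).
- Window examined: the first 12 weeks on the full app.

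**Rule.** For an arm starting at week s, count the questions in the interval from s (excluded) to s + 12 (included). Take each gap back to the previous question or, for the first, to s.

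**Intervention arm, s = 0.** Questions at 4, 8 and 12: three. Gaps: 4 − 0 = 4, 8 − 4 = 4, 12 − 8 = 4 weeks.

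**Control arm, s = 12.** Window 12 to 24. Question at 24: one. Gap: 24 − 12 = 12 weeks.

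The first solicited report after exposure therefore comes at 12 weeks instead of 4, which is 12 / 4 = 3 times later, and from one question instead of three.

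**With questions added at weeks 16 and 20.** Control arm: questions at 16, 20 and 24; gaps 16 − 12 = 4, 20 − 16 = 4, 24 − 20 = 4 weeks. This matches the intervention arm.

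**The synopsis discrepancy.** If the Safety row, with weeks 4, 8 and 12 only, were read as the whole schedule, the control count would be zero. The time-points row and Table 1 give one. The Safety row may be meant for the DiGA period alone, but it does not say so.

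**Other routes, side by side with the gap**
- Serious suspected reactions: phone call at any time, with measures within 48 hours (section 9). Covered, if the patient calls.
- Non-serious suspected reactions: contact information only (section 5.5). No scheduled question between weeks 12 and 24.
- Serious events not linked to the app by the patient: the phone instruction does not address them. No scheduled question between weeks 12 and 24.

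**The case against.** The strongest reply is that the follow-up lies outside the study under review. The synopsis, SAP sections 1 and 3 and the footnote to SAP Table 1 all say so. Its stated purpose is 24-week data in the intervention arm and motivation of controls, and no planned analysis pools the two arms' first-exposure data. This stands as a limit on the consequence. It does not remove the point, because this protocol's own Table 1 sets collection through week 24, and a later SAP cannot supply answers to questions that were not asked.

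A second reply is that other channels exist and that the risk is expected to be low. That also stands in part: serious suspected reactions have their own route, and device risk management continues during the study. The event log is evaluated every 3 months, so 4-weekly questions would not necessarily speed central review.

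Three stronger readings are tempting, and the documents do not support them.

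- **That half the exposed safety data is lost.** A reader might compare zero-event one-sided 95% upper bounds, 1 − 0.05^(1/173) = 1.7% and 1 − 0.05^(1/346) = 0.9%, and credit the difference to extra questions. The bound depends on the number of patients, not of questions. The week-24 answers can already give a 12-week total for up to 346 patients, so no such gain is claimed.
- **That the plan breaks its own rule for new users.** Weeks 4, 8 and 12 are times since randomization, applied to both arms. Nothing defines them by time since first access to the full app.
- **That a 12-week recall period is specified.** The wording of the follow-up question is not given; 12 weeks is the gap between questions. The follow-up column is also marked for app usage, which is not a single-day measurement, so a single question at week 24 is the likeliest reading rather than an explicit statement.

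**Conclusion.** The point holds as a cheap improvement to the follow-up phase: one solicited safety question against three, and a first question at 12 weeks after exposure against 4. The losses are confined to timely solicited capture of non-serious suspected reactions and of serious events not attributed to the app, to their timing in 4-week windows, and to reports from controls who stop early. The primary analysis and the 12-week safety comparison do not change.

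The conclusion rests on reading the 24-week column as a single assessment and on controls starting the full app at week 12. How many controls would stop before week 24 is not given, so the number of missed reports cannot be sized. Protocol section 5.1 ties the participant fee to 12 weeks of documentation and mentions none for follow-up, so some loss is plausible.

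**What to change.** 1. In protocol Table 1 and the synopsis, add the existing in-app safety questions at weeks 16 and 20, at least in the control group. Intervention patients already have their first 12 weeks covered, so including them is optional.
2. In the follow-up SAP, tabulate suspected reactions by time since first access to the full app.
3. In the same edit, reconcile the synopsis Safety row with the time-points row and Table 1, so that all three show the same schedule or state which study period they cover.

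The cost is two more short automatic questionnaires per patient in follow-up, with no added visits or staff. The drawback is slightly more patient burden. The change should be in place before the first controls cross over. With first randomization planned for January 29, 2021, 12 weeks (84 days) later is April 23, 2021. The follow-up SAP is due only in the first half of that year, so the schedule should not wait for it.
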